# A comparison between the effects of school‐based education programs provided by peer group versus health practitioners on premenstrual syndrome in adolescents: A protocol for a non‐masked clinical trial

**DOI:** 10.1002/nop2.858

**Published:** 2021-03-14

**Keywords:** adolescent, health practitioner, peer educator, peer group, PMS, premenstrual syndrome, school‐based

## Abstract

**Aim:**

To compare the effect of school‐based education programs, by peer group versus health practitioner on Premenstrual Syndrome (PMS) in adolescent girls.

**Design:**

Non‐masked three‐armed clinical trial.

**Methods:**

Ninety 11th‐grade students with moderate to severe PMS will be allocated to Intervention Group 1 (IG1), Intervention Group 2 (IG2) and Comparison Group (CG). Three weeks (six online sessions) of parallel education will be implemented in IG1 by trained peer educators and in IG2 by a health practitioner. The primary outcome will be changes in PMS severity score between three groups over time (measured by Daily Record of Severity of Problems). Secondary outcomes include changes in Premenstrual Dysphoric Disorder and General Health. Data collection will be conducted in two‐time points, at baseline, and at the end of the intervention.

**Results:**

Our study will explore the effect of school‐based education programs, by peer group versus health practitioner on PMS. This will add to the evidence‐based interventions to PMS management and the effectiveness of peer education in health promotion of adolescents girls.

## BACKGROUND

1

Premenstrual Syndrome (PMS) is an important health concern in adolescence that can significantly interfere with daily life activities and has a wide variety of physical and psychological signs and symptoms (Abeje & Berhanu, 2019; Mishra et al., 2015; Tadakawa et al., 2016). The American College of Obstetricians and Gynecologists (ACOG) has well‐established some criteria in describing PMS, including emotional symptoms (such as depression, angry outbursts, anxiety, irritability, crying spells, confusion, social withdrawal, poor concentration, insomnia, increased nap‐taking and changes in sexual desire) and physical symptoms (such as thirst and appetite changes, food cravings, breast tenderness, bloating and weight gain, headache, swelling of the hands or feet, aches and pains, fatigue, skin problems, abdominal pain and gastrointestinal symptoms). ACOG has also stated that the symptoms must be present in the 5 days before the menstrual cycle for at least 2–3 months, end within 4 days after the period starts, interfere with some of the females' normal activities, and not relapse until after day 12 of the menstrual cycle (ACOG Practice Bulletin, 2001). Although these symptoms may be not life‐threatening, they can seriously affect adolescents' learning activities as well as their mental health, interpersonal relationships and quality of life, that all of these are health‐related concerns worldwide (Buddhabunyakan et al., 2017; Delara et al., 2013; Kues et al., 2014). Existing literature has reported a 10% to 80% prevalence of PMS in adolescents worldwide and 40% to 80% in Iranian adolescents (Abeje & Berhanu, 2019; Delara et al., 2013; Ranjbaran et al., 2017; Tadakawa et al., 2016). Despite the high prevalence of PMS and the fact that adolescents with lower awareness about menstrual‐related problems showed a higher prevalence of menstrual disorders, their awareness about this issue is low (Seedhom et al., 2013).

Nowadays, for the management of PMS, various medical and non‐medical interventions are recommended (Appleton, 2018; Bahrami et al., 2018; Heydari et al., 2019; Maleki‐Saghooni et al., 2018; Tully et al., 2020; Yilmaz‐Akyuz & Aydin‐Kartal, 2019). Some studies have shown that education about changes in lifestyle; proper nutrition; and stress reduction techniques can be effective and even as the first step for PMS management (Aşcı et al., 2015; Steiner, 2000; Taghizadeh et al., 2010). One of the effective ways to educate adolescents is peer‐group education (Ghasemi et al., 2018). Peer education is a participatory teaching or sharing style in which people of similar social backgrounds, life experiences or group membership (peers) educate each other about specific topics (Southgate & Aggleton, 2016). One of the positive aspects of this method in adolescence is creating interaction between peers to exchange information since they spend most of their lives in schools and have a high impact on their classmates (Ghasemi et al., 2018; Lejone et al., 2020). Strengthening the critical thinking of adolescents, changing health attitudes, peers' good understanding from the surrounding social and cultural environment, and increasing self‐confidence are the other benefits of this approach (Seymour et al., 2013; Tolli, 2012). A well‐trained peer can communicate with others properly and effectively and in ways that the healthcare providers may be not able to do (Lotfi Mainbolagh et al., 2013). Therefore, replacing trained peers with healthcare providers in order to educate health‐related concepts for adolescents is a good opportunity (Campbell et al., 2014).

A review of the literature shows the effectiveness of peer education in HIV/AIDS prevention, sexual and reproductive health promotion, and drug and tobacco use cessation (Benton et al., 2020; Ghasemi et al., 2018; MacArthur et al., 2016; Sun et al., 2018). To the best of our knowledge, little is known about the effect of peer‐group education on PMS. If it is documented that educating adolescents by peers and health practitioner will have a similar effect on PMS, the available and cost‐effective peer educators can be used instead of the health practitioners. Therefore; this study aims to compare the effect of a school‐based education program by peer group versus health practitioner on PMS in adolescents.

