### Objectives and research hypothesis

1.1

The primary objective of this study is to compare the effectiveness of a school‐based education program by peer group versus health practitioner on PMS severity in adolescents that will be measured by Daily Records of Severity of Problems (DRSP). The secondary objectives are the effectiveness of the mentioned intervention on Premenstrual Dysphoric Disorder (PMDD) and General Health (GH) of the target group. The study has two main hypotheses: (1) We expect that education by peer group has a similar effect as education by health practitioner on PMS; (2) We expect the more reduction of PMS severity in intervention groups versus the comparison group.

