### Sample size

2.5

Sample size will be determined at CI: 95% and Power: 80%, Large Cohen effect size = 0.8, in the intervention group, compared to the control group, and by the assistance of following formula:
$$n=\frac{2*{\left(z1‐\frac{\alpha }{2}+z1‐\beta \right)}^{2}}{E{\text{.S}}^{2}}=\frac{2*{\left(1.96+0.84\right)}^{2}}{{\left(0.8\right)}^{2}}=25.$$
z0.975=1.96z0.8=0.84.

By considering an attrition rate 25%, the sample size in each group will be calculated, 30 students.

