### Statistical analysis

2.10

All analyses of the outcomes will performed as intention‐to‐treat analyses and following the TREND checklist. The normality of distribution will be examined by the Kolmogorov–Smirnov test. All quantitative variables will be expressed as mean ± *SD*. Categorical variables will be presented as frequencies and percentages. The chi‐square test will be used to test for differences between categorical variables. Baseline means differences will be tested using a one‐way analysis of variance (ANOVA or the non‐parametric equivalent of that Kruskal–Wallis). Analysis of covariance (ANCOVA) will be used to identify differences between the three groups at the end of the study, adjusting for baseline values and covariates. The comparison of mean values will be conducted within groups after the intervention period using paired sample *t* tests. *p* < .05 will be considered statistically significant. Statistical tests of the outcome measures will be performed using Statistical Package for the Social Sciences (SPSS version 18.0).

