## DISCUSSION

3

To the best of our knowledge, this is the first trial that will investigate the effectiveness of a school‐based peer‐group education versus health practitioner on PMS in adolescents. This study aims to address several gaps in the current scientific evidence for educational intervention and optimal use of adolescent's capabilities. Firstly, until now there have been a limited number of studies that investigate the effectiveness of peer‐group education on PMS, particularly in adolescents. Secondly, this comparison study between peer educators and health practitioner aims to use peer educators as an alternative to a health practitioner in areas with less access to healthcare providers in schools. This study evaluates the response of education by two different trainers, peer group and health practitioner, aims to use peer group instead of health practitioner to improve peers' ability on PMS management in the adolescents. To conclude, if the peer education intervention improves PMS, there is potential for the program to be widely implemented by schools resulting in a saves time and cost which is needed for healthcare providers training. Finally, with the utilization of peer‐group education, we will have a positive impact on adolescent population health.

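### Similar results with peers and practitioners are allowed to justify replacement without requiring that either programme beats the comparison group

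*Protocol article*

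**What the plan says.** The trial compares peer education (IG1), practitioner education (IG2) and a comparison group (CG).

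- **Background.** The rationale for the trial is conditional on one thing: if it is shown that peers and practitioners "will have a similar effect on PMS, the available and cost‐effective peer educators can be used instead of the health practitioners". The comparison group does not appear in that sentence. The stated aim follows directly from it.
- **Section 1.1.** The first main hypothesis is "We expect that education by peer group has a similar effect as education by health practitioner on PMS". The second is "We expect the more reduction of PMS severity in intervention groups versus the comparison group". The two are listed side by side, with no order and no dependence of one on the other.
- **Section 2.10.** "Analysis of covariance (ANCOVA) will be used to identify differences between the three groups at the end of the study", with adjustment for baseline values and covariates. There are also paired tests: "The comparison of mean values will be conducted within groups after the intervention period using paired sample" *t* tests. The threshold is *p* "< .05 will be considered statistically significant". No equivalence or non-inferiority test is described.
- **Section 2.5.** The sample size is set for "Power: 80%, Large Cohen effect size = 0.8, in the intervention group, compared to the control group", which is the contrast with the comparison group and not peer against practitioner.
- **Discussion.** "if the peer education intervention improves PMS, there is potential for the program to be widely implemented by schools". What the improvement is measured against is not said. Other sentences of the Discussion state the aim of using peers in place of practitioners without this condition.

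**The concern.** Similarity of two programmes supports replacing one with the other only if the one being replaced works. Two programmes that do nothing have a true difference of exactly zero, so they are as similar as two programmes can be. An inference that looks only at IG1 against IG2 cannot tell equally effective from equally ineffective. The trial has the arm that could tell them apart, but the text does not make its result a condition.

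At stake is the main practical conclusion. A trial in which neither programme improved on routine school counselling could be reported as showing that peers can take over from practitioners. The planned paired *t* tests add to the risk. PMS scores may fall from baseline in all three arms for reasons unrelated to the education, and a significant fall within the peer arm could then be taken as the improvement that the Discussion asks for.

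**Working it through.** **Inputs.** Two-sided alpha .05 (section 2.10, and z = 1.96 in section 2.5). Planned effect d = 0.8 and 25 or 30 students per arm (section 2.5). Three schools randomised to three arms, read as one school per arm (section 2.6). Two inputs are assumptions because the article does not give them: similar means two-sided p ≥ .05 for IG1 against IG2, and the between-school intraclass correlation ρ is 0 to 0.10.

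**The plan's own figure.** n = 2(1.96 + 0.84)²/0.8² = 15.68/0.64 = 24.5, rounded up to 25. This reproduces, and it confirms that the trial was sized for the contrast with the comparison group.

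**Step 1: no effect in any arm, independent students.** P(similar) = P(|Z| < 1.96) = 0.95 at any n. This is simply 1 − alpha.

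**Step 2: the same with one school per arm and a test that ignores school.** The true standard error of the difference is √[2(ρ + (1 − ρ)/n)], while the test uses about √[2(1 − ρ)/n]. Hence

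P(similar) = 2Φ(1.96 × √{[(1 − ρ)/n] / [ρ + (1 − ρ)/n]}) − 1.

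- n = 25, ρ = 0.02: 0.0392/0.0592 = 0.662, square root 0.814, times 1.96 = 1.595, so P = 0.889.
- n = 30, ρ = 0.10: 0.030/0.130 = 0.231, square root 0.480, times 1.96 = 0.942, so P = 0.654.

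**Step 3: add the missing condition.** Simulation of 400,000 trials per setting: three arm means, pooled error variance with 3(n − 1) degrees of freedom, two-sided .05 tests. Ranges cover n = 25 and n = 30.

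| Truth | ρ | Similar only | Similar and IG2 beats CG | Similar and both beat CG |
|---|---|---|---|---|
| No effect | 0 | 95% | 2% | 0.5% |
| No effect | 0.02 | 88–89% | 4% | 1–2% |
| No effect | 0.05 | 78–81% | 6–7% | 3–4% |
| No effect | 0.10 | 66–69% | 9–10% | 5–6% |
| Both 0.8 SD | 0 | 95% | 76–83% | 67–76% |
| Both 0.8 SD | 0.05 | 78–81% | 59–61% | 51–55% |

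Without the condition and with independent students, the similarity reading gives the same 95% whether both programmes fail or both work at 0.8 SD. It carries no information about whether there is an effect to preserve.

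**Step 4: how much of the 95% is due to the missing margin.** Replace p ≥ .05 by two one-sided 5% tests against an assumed margin, with no effect in any arm and independent students. Two null programmes pass in 0.1–1% of trials at a margin of 0.4 SD, 10–22% at 0.5 SD and 75–85% at 0.8 SD (n = 25 and 30). So most of the 95% comes from reading non-significance as similarity. The missing effect check remains a flaw at any margin, because a true difference of zero lies inside every margin and a larger trial would pass two null programmes more often.

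**The case against.** The strongest reply is that the Background sentence is rationale, not a decision rule. Section 2.10 contains no replacement rule. The comparison group is central to the design: superiority over it is one of two main hypotheses, the primary outcome is compared across three groups, and the sample size is built on it. The Discussion does make implementation depend on benefit. The Background also speaks of similarity being documented, which can be read as asking for positive evidence. Finally, ordering hypotheses is often left to an analysis plan, which is not shown.

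Much of this stands as a limit on the point. A reader might infer that the protocol has no effectiveness condition at all; the second hypothesis and the Discussion show otherwise. A reader might also take 95% as a property of this trial. It is not: it is 1 − alpha under a definition of similar that the protocol never states, and with independent students.

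What does not stand is that the condition is already met. The second hypothesis will be tested, but if it fails and the educated arms look alike, nothing in the text stops the replacement claim. The Discussion's condition has no comparator and concerns only the peer programme, not whether the practitioner programme worked. The issue is also not merely detail left to an analysis plan, because the inference from similarity to replacement is written out in the current text.

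**Conclusion.** The point holds as a gap between statements that are each reasonable: the replacement inference, the superiority hypothesis and the implementation condition are not joined. As written, a null trial can support replacement.

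If similar means p ≥ .05, this happens in up to 95% of null trials with independent students, and in about 66–89% with one school per arm, an unadjusted test and an assumed ρ of 0.02–0.10. Both the definition and the ρ range are assumptions.

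A further tempting inference is that a margin would leave these rates unchanged. The calculation does not support that: at margins of 0.4–0.5 SD two null programmes would pass in only 0.1–22% of trials. The size of the problem therefore comes mostly from the missing equivalence test. The absent effect check is a separate, conceptual flaw, which a margin alone does not repair. The protocol should be changed on this point.

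**What to change.** - **Sections 1.1 and 2.10:** order the hypotheses. Test the baseline-adjusted IG2–CG and IG1–CG contrasts first. Interpret IG1–IG2 similarity as support for replacement only if IG2 is superior to CG, and recommend peers only if IG1 is also superior to CG. Otherwise state that similarity is uninterpretable and make no replacement claim. Do not let the within-group paired *t* tests count as evidence for either condition.
- **Background and Discussion:** use the same conditional wording, and name the comparison group as the comparator for improvement in the Discussion.

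This needs no new data and no extra students. The contrasts come from the ANCOVA already planned.

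The cost is a claim that is harder to reach. When both effects are truly 0.8 SD and students are independent, it is reached in 67–76% of trials if both arms must beat CG, or 76–83% if only IG2 must, and less often with clustering. The protection is also weaker with clustering: requiring IG2 to beat CG leaves 4–10% false replacement at ρ of 0.02–0.10, against 2% with independent students. The ordering does not solve the one-school-per-arm problem, and it does not replace a defined margin for similar, which has to be set separately.

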### Objectives and research hypothesis

1.1

The primary objective of this study is to compare the effectiveness of a school‐based education program by peer group versus health practitioner on PMS severity in adolescents that will be measured by Daily Records of Severity of Problems (DRSP). The secondary objectives are the effectiveness of the mentioned intervention on Premenstrual Dysphoric Disorder (PMDD) and General Health (GH) of the target group. The study has two main hypotheses: (1) We expect that education by peer group has a similar effect as education by health practitioner on PMS; (2) We expect the more reduction of PMS severity in intervention groups versus the comparison group.

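### The hypothesis that peer and practitioner education have similar effects has no matching analysis or sample size: the article tests only for differences and is sized only for intervention versus control

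*Protocol article*

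**What the plan says.** The Objectives section of the protocol article makes the primary objective to "compare the effectiveness of a school‐based education program by peer group versus health practitioner on PMS severity". Two main hypotheses follow. The first is "We expect that education by peer group has a similar effect as education by health practitioner on PMS". The second is "We expect the more reduction of PMS severity in intervention groups versus the comparison group".

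The Background attaches a decision to the first: "If it is documented that educating adolescents by peers and health practitioner will have a similar effect on PMS", peer educators can take the practitioners' place.

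The Sample size section has one calculation, at 95% confidence and 80% power, for a "Large Cohen effect size = 0.8, in the intervention group, compared to the control group". It arrives at 25 per group and, after an allowance for attrition, 30.

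The Statistical analysis section states: "Analysis of covariance (ANCOVA) will be used to identify differences between the three groups at the end of the study", adjusted for baseline values and covariates. Its only decision criterion is p < .05.

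**The concern.** Hypothesis 2 is a superiority claim, and both the test and the sample size suit it. Hypothesis 1 is a claim of similarity, and neither suits it. A test for differences can show that two arms differ; failing to reject does not show that they are alike. Similarity needs a stated limit for an unimportant difference, and an interval or test judged against that limit. The three-group ANCOVA does not fill the gap either. Its overall result may be driven by the comparison group and need say nothing about peers (IG1) versus practitioners (IG2).

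The mismatch falls on the comparison named as the primary objective. With at most 30 students per arm, a non-significant IG1–IG2 result would be common even if peers were materially worse. If it were taken as similarity, it could support replacing practitioners on evidence that does not bear on the question.

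**Working it through.** **Inputs from the article.** Two-sided alpha 0.05, power 80%, standardised difference 0.8 for intervention versus control, attrition 25%, and 30 per group (Sample size section).

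**Assumptions made here.** Independent students with no school effect; a true peer deficit of 0.4 SD (half of the planned 0.8); margins of 0.3 to 0.5 SD; a baseline–outcome correlation of either zero (unadjusted) or 0.6. The article gives no margin and no correlation.

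**The article's own figure.** n = 2 × (1.96 + 0.84)² / 0.8² = 15.68 / 0.64 = 24.5, rounded up to 25. It reproduces, for intervention versus control. No calculation addresses IG1 versus IG2.

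**Arm sizes examined.** 30 as planned; 25 as the formula requires; 22 as what remains of 30 after 25% attrition (30 × 0.75 = 22.5).

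**Step 1: standard error of IG1–IG2 in SD units.** SE = √(2/n), giving 0.258, 0.283 and 0.302 for n = 30, 25 and 22. A correlation of 0.6 multiplies the SD by √(1 − 0.36) = 0.8, giving 0.207, 0.226 and 0.241.

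**Step 2: chance of p > .05 when peers are 0.4 SD worse.** This is one minus the power of a two-sided pairwise t test (non-central t, 2n − 2 degrees of freedom, non-centrality 0.4/SE).

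**Step 3: 95% CI half-width.** t(0.975; 2n − 2) × SE. For n = 30: 2.002 × 0.258 = 0.517 SD.

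**Step 4: non-inferiority power if the arms are truly equal.** Φ(margin/SE − 1.96). For n = 30, unadjusted, margin 0.3: Φ(1.16 − 1.96) = 21%; margin 0.5: Φ(1.94 − 1.96) = 49%.

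| n per arm | Baseline correlation | P(p > .05), peers 0.4 SD worse | 95% CI half-width (SD) | Non-inferiority power, margin 0.3 to 0.5 SD |
|---|---|---|---|---|
| 30 | 0 | 67% | 0.517 | 21–49% |
| 25 | 0 | 72% | 0.569 | 18–42% |
| 22 | 0 | 75% | 0.608 | 17–38% |
| 30 | 0.6 | 52% | 0.413 | 31–68% |
| 25 | 0.6 | 59% | 0.455 | 26–60% |
| 22 | 0.6 | 63% | 0.487 | 24–55% |

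**Step 5: two-sided similarity.** For both 95% bounds to lie inside ± margin, the half-width must be smaller than the margin. Unadjusted, every half-width exceeds 0.5 SD, so no margin up to 0.5 SD could be met if the SD is as assumed. With correlation 0.6, every half-width exceeds 0.4 SD.

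**Step 6: which margin fits the planned size.** With no adjustment, 80% non-inferiority power needs 175, 99 and 63 evaluable per arm at margins of 0.3, 0.4 and 0.5 SD. The planned size fits only a margin near 0.8 SD (25 evaluable per arm), which is the whole of the planned benefit.

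**The case against.** *The article never says that p > .05 will count as similarity.* Correct. A reader might infer such a rule because p < .05 is the only criterion given, but the text does not contain it. It stands as a risk. The mismatch between hypothesis, test and sizing does not depend on it.

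*Replacement does not hang on similarity alone.* Also correct. The Discussion gives another route: if peer education improves PMS, schools could adopt it widely, with peers as an alternative where access to providers is poor. That route rests on IG1 versus the comparison group, the kind of contrast that was sized. So a reader should not infer that every use of the results depends on hypothesis 1. The Background's route does, and so does the primary objective.

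*The planned analysis is baseline-adjusted, so unadjusted figures are too pessimistic.* In part. With correlation 0.6 and 30 per arm, p > .05 at a 0.4 SD deficit is close to a coin toss (52%). If peers lost the whole 0.8 SD, p > .05 would occur in only about 14% of trials at n = 30, even unadjusted. It would be too strong to say that a non-significant result is near-certain whatever the truth. Adjusted non-inferiority power still stays below 80% at every margin examined.

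*A margin belongs in the analysis plan or the full protocol.* Details of a margin may sit there. But the article itself fixes the hypothesis, the test and the contrast used for sizing. A margin for IG1 versus IG2 would have had to enter the sample size, which rests on another contrast.

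*The wording of the hypothesis is only an expectation.* It is labelled a main hypothesis, matches the primary objective and supports a stated decision.

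**Conclusion.** The point holds. Hypothesis 1, the primary objective and the replacement argument in the Background call for an equivalence or non-inferiority inference, and the article's stated test and sample size cannot supply one.

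The size of the shortfall depends on the margin and the baseline correlation, both assumed here. Across margins of 0.3 to 0.5 SD, non-inferiority power runs from 17% (22 per arm, unadjusted) to 68% (30 per arm, correlation 0.6). The conclusion is the same throughout that range.

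All figures assume independent students and no school effect. The Recruitment and randomization section allocates three schools, one to each arm, so the figures are optimistic. For the same reason, even a narrow student-level interval for IG1–IG2 could not separate the effect of the educator from that of the school.

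**What to change.** In section 2.10 (Statistical analysis), make the baseline-adjusted IG1–IG2 difference in DRSP severity, with its 95% CI, the analysis for hypothesis 1, and state that p > .05 is not evidence of similarity. Then choose one of two courses:

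- **(a)** Fix a justified margin in DRSP points before outcome data are seen. Claim that peers are not worse (non-inferiority) only if the CI bound on the unfavourable side is within the margin. Claim that the effects are similar (equivalence) only if both bounds are. Otherwise report the result as inconclusive.
- **(b)** Drop the similarity claim and report the estimate with its CI only.

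Test hypothesis 2 with the IG1–CG and IG2–CG contrasts from the same ANCOVA.

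In section 2.5 (Sample size), state that the 80% power refers only to intervention versus control and that power for hypothesis 1 is low. Add that, with one school per arm, a student-level CI inside the margin cannot separate educator effect from school effect.

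The cost is wording and, under (a), one pre-specified margin; no extra data are needed. The downside is that the likely conclusion on hypothesis 1 becomes inconclusive. The Trial status section says that recruitment is still ongoing, so a margin has to be settled promptly to be credible.
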